### Outcome assessments

The primary outcome for treatment-resistant depressed patients (study 1) is depression severity as measured with the HDRS-17 [1] at week 9. Global Assessment of Function (GAF) scores at week 9 will be reported in addition to the primary outcome. The secondary outcome is remission defined as HDRS score ≤ 8 at week 9. Confidence intervals will be reported in relation to the proportions in remission. The tertiary outcomes are memory and executive functions, measured with the Rey Auditory Verbal Learning Test (RAVLT) [2,3] and Rapid Visual Processing (RVIP) test from the Cambridge Neuropsychological Test Automated Battery (CANTAB), respectively, facial expression recognition measured with a facial expression recognition test, as well as self-ratings of cognitive difficulties on the CPFQ, depressive symptoms and life quality at week 9.

For bipolar patients in remission (study 2) the primary outcome is memory performance measured with the RAVLT at week 9. The secondary outcome is sustained attention measured with the RVIP test and recognition of emotional facial expressions assessed with a facial expression recognition test at week 9. Finally, the tertiary outcomes are ratings of mood, symptoms, quality of life and cognitive function at week 9.

Clinical mood ratings and patients' self-ratings will be performed at baseline, and weeks 5, 9 and 14 to assess the speed and duration of potential effects on these measures. Neuropsychological testing is performed at baseline, and weeks 9 and 14 to assess effects of Epo vs. placebo treatment and their duration. For overview see table 1.

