### Sample size and power calculation

Sample size and statistical power for the two studies were calculated using nQuery Advisor 5.0 software. The primary outcome in study 1 is depression severity reflected by HDRS-17 after Epo vs. placebo treatment. The clinically relevant difference is defined as minimum 3 scores on this scale. The mean standard deviation in the two treatment groups is estimated to be 3 HDRS-17 scores and the mean scores to be 18 and 21 after Epo and placebo treatment, respectively. With these assumptions a sample of n = 40 patients (n = 20 per drug group) has a statistical power of 86% to detect a clinically relevant difference in HDRS-17 scores between the two treatment groups at an alpha level of 5% (2-sided test).

The primary outcome in study 2 is verbal memory, reflected by the RAVLT total score after Epo vs. placebo treatment. A recent study has shown that the mean RAVLT total score for patients with bipolar disorder in remission is 52.0 (while the mean score for healthy age-matched controls was 60.7) out of a maximum of 75 [47]. We estimate that a clinically relevant difference between drug groups in the change in RAVLT scores is at least 4 points (half-way to normal function). The mean standard deviation in RAVLT scores in the two treatment groups is estimated to be 4 points and the mean scores to be 56 and 52 after Epo and placebo treatment, respectively. With these assumptions a sample of n = 40 patients (n = 20 per drug group) has a statistical power of 86% to detect a clinically relevant difference in RAVLT total scores between the two treatment groups at an alpha level of 5% (2-sided test).

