### Statistical analyses

Data will be collected until dropout from all randomised patients and analysed using repeated measures analysis of variance (ANOVA). Significant interactions were analysed further with simple main effect analyses. In the case of missing or invalid data, we will perform Per Protocol (PP) analyses for complete data sets and Intention to Treat (ITT) analysis. In the case of disparity between the results of these analyses, the outcome of the ITT analysis will be regarded as the result of the study. The statistical threshold for which results are considered significant if p ≤ 0.05 (2-tailed). Statistical analyses will be performed using the Statistical Package for Social Sciences (SPSS).

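### The primary outcomes are week-9 scores and the 86% power is that of a two-group comparison of means, but the only named analysis is repeated measures ANOVA, with no term tied to week 9

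*Protocol article*

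**What the plan says.** Three sections of the protocol article bear on this.

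- **Outcome assessments.** For study 1 the primary outcome "is depression severity as measured with the HDRS-17 [1] at week 9". For study 2, "the primary outcome is memory performance measured with the RAVLT at week 9". On timing: "Clinical mood ratings and patients' self-ratings will be performed at baseline, and weeks 5, 9 and 14", and "Neuropsychological testing is performed at baseline, and weeks 9 and 14". HDRS-17 therefore has four measurements and RAVLT three. Week 14 falls in the treatment-free period of Table 1.
- **Sample size and power calculation.** Study 1 assumes means of 18 and 21 with SD 3; study 2 assumes 56 and 52 with SD 4. Each has 20 patients per group and a two-sided 5% level. For study 1 the conclusion is that the sample "has a statistical power of 86% to detect a clinically relevant difference in HDRS-17 scores between the two treatment groups", and the same 86% is given for study 2. No between-visit correlation, number of visits or time course enters.
- **Statistical analyses.** Data are "analysed using repeated measures analysis of variance (ANOVA). Significant interactions were analysed further with simple main effect analyses". The section lists no factors or visits, does not say which term decides the primary hypothesis, and mentions no direct comparison at week 9.

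**The concern.** The outcome and power sections describe one comparison: Epo against placebo at a single time point. The analysis section names a method that yields several tests (group, time, and their interaction) and mentions time-specific comparisons only as a follow-up to a significant interaction.

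Two things are at stake. First, the 86% cannot be attached to the named method without a correlation and a time course, and the article gives neither. Second, if week 9 is reached only through a significant interaction, a real week-9 effect of the planned size can be missed because the overall profile test falls short. With no deciding term named, it is also open which result would be reported as the answer to the primary question.

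**Working it through.** **Inputs from the article:** 20 per group; standardised difference 3/3 = 4/4 = 1.0; two-sided 5%; HDRS-17 at four visits, RAVLT at three.

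**Assumptions, because the article gives no values:** equal between-visit correlation ρ of 0.3, 0.5 or 0.7, equal SD at all visits, complete data, and two time courses of the arm difference, both with the planned effect at week 9:

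- Study 1 (baseline, weeks 5, 9, 14): fading 0, 1.5, 3, 1.5 points; sustained 0, 1.5, 3, 3 points.
- Study 2 (baseline, weeks 9, 14): fading 0, 4, 2 points; sustained 0, 4, 4 points.

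**Step 1: the stated power.** For a two-sample t-test the noncentrality is d·√(n/2) = 1·√10 = 3.16 on 38 df, and power is 86.9%. The stated 86% is reproduced for both studies.

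**Step 2: group-by-time interaction over all visits.** The noncentrality is λ = (n/2)·Σ(dₜ − d̄)²/(1 − ρ), with dₜ in SD units, on T − 1 and 38(T − 1) df for T visits. Example, study 1 fading: d = 0, 0.5, 1, 0.5; d̄ = 0.5; sum of squares 0.5; at ρ = 0.5, λ = 10 × 0.5/0.5 = 10 on 3 and 114 df, which gives 74.5%.

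**Step 3: interaction and week-9 t-test both significant.** These are simulated probabilities, 20,000 trials per scenario.

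| Scenario | Interaction alone, ρ = 0.3 / 0.5 / 0.7 | Interaction and week 9 |
|---|---|---|
| Study 1, fading | 58.3 / 74.5 / 93.6% | 55 / 68 / 83% |
| Study 1, sustained | 73.7 / 87.8 / 98.6% | 66 / 78 / 86% |
| Study 2, fading | 64.6 / 79.9 / 95.7% | 61 / 73 / 84% |
| Study 2, sustained | 77.8 / 90.4 / 99.0% | 70 / 80 / 86% |

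The last column cannot exceed 86.9%, because it requires the week-9 test to succeed as well.

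**Step 4: only baseline and week 9 enter.** The interaction is then the t-test on change scores, with standardised effect 1/√(2(1 − ρ)) = 0.845 / 1.000 / 1.291. Power is 74.0 / 86.9 / 97.8%. It equals the Step 1 figure only at ρ = 0.5.

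**Step 5: the group main effect decides.** The standardised effect is d̄/√((1 + (T − 1)ρ)/T). For study 1 fading at ρ = 0.5 this is 0.5/√(2.5/4) = 0.632, and power is 49.6%. At ρ = 0.3 and 0.7 it is 60.9% and 41.7%.

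**Step 6: a direct week-9 contrast.** Unadjusted, power is 86.9%, as in Step 1. Adjusted for baseline, the residual SD falls by a factor √(1 − ρ²), and on 37 df power is 89.8 / 94.5 / 99.1%.

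**The case against.** The strongest reply is that the analysis section says less than this point might be taken to claim. It does not state that all visits enter, that the interaction decides, or that week 9 goes untested when the interaction is not significant. The Outcome assessments section gives the other mood ratings a purpose of their own (they "will be performed at baseline, and weeks 5, 9 and 14 to assess the speed and duration of potential effects"), and the sample-size text describes the study 2 target as a difference in change. Both fit a baseline-to-week-9 ANOVA, which addresses week 9 directly and has no omnibus gate. A journal article may also leave the list of visits to a fuller document.

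Much of this stands. The gate and the use of all visits are the natural reading, not explicit rules, and the losses in Step 3 depend on that reading. The objection does not remove the mismatch: even the two-visit ANOVA has the stated power only at one correlation, which the article never gives. Nor does the point rest on silence alone. The article states an outcome time point, a power basis and a method, and the method is not the one that was powered.

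Two stronger inferences are tempting, and the documents support neither. One is that the named analysis is always weaker: with a sustained effect and a correlation of 0.5 or more, the interaction test alone exceeds 86%, although it answers a wider question. The other is that a difference only at week 14 would produce a false claim on the primary outcome. A significant interaction leads only to follow-up comparisons, and the primary outcome is still defined at week 9. Requiring an extra test first cannot raise the week-9 error rate above 5%.

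**Conclusion.** The point holds as a mismatch between stated parts of the article. The outcome and the 86% belong to a two-group comparison at week 9; the analysis section names repeated measures ANOVA and ties none of its terms to that comparison.

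The size is conditional. On the natural reading, the chance of a positive week-9 result falls from about 87% by roughly 20 to 32 points in study 1 and 17 to 26 in study 2 at a correlation of 0.3. At 0.7 the loss is only about 1 to 4 points. On the two-visit reading, power may lie below or above the stated figure. All these values rest on assumed correlations, equal correlation between visits, and assumed effects at weeks 5 and 14. They show how far the answer depends on what is left open; they do not establish that the trial is underpowered, and no inflation of the week-9 type I error has been shown.

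**What to change.** In the Statistical analyses section, state that each primary hypothesis (HDRS-17 in study 1, RAVLT total score in study 2) is decided by one between-arm contrast at week 9, preferably adjusted for the baseline score already collected, tested once at two-sided 5% whether or not any interaction is significant. Describe the group-by-time interaction and the other visits as supportive. In the sample-size section, say that the 86% refers to this contrast.

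The cost is a sentence or two in each place, written before unblinding. No new data or patients are needed. The unadjusted contrast keeps the stated power, and baseline adjustment would raise it at each correlation considered (Step 6). The interaction loses any deciding role.

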### Randomisation

Block randomisation for the two studies has been performed by Pharma Consulting Group AB http://www.pharmaconsultinggroup.com. Pharma Consulting Group has created randomisation lists for each study and emergency envelopes for each patient ID number. Treatment groups are stratified for age (< or ≥ 35 years) and gender. Upon inclusion of participants, the date of birth, gender, diagnosis, and to which of the above strata the participant belongs are recorded. Numbering within each stratum is consecutive and study identification numbers are recorded in the patients' individual case report forms (CRFs).

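### Both primary outcomes are week-9 scores and the 86% power is that of a week-9 t-test, but the named repeated-measures ANOVA does not make the week-9 contrast the deciding test

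*Protocol article*

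**What the plan says.** **Target.** Under Outcome assessments, the primary outcome of study 1 is the HDRS-17 at week 9. For study 2: "For bipolar patients in remission (study 2) the primary outcome is memory performance measured with the RAVLT at week 9". The same section and Table 1 schedule the HDRS-17 at four visits (baseline, weeks 5, 9 and 14) and the RAVLT at three (baseline, weeks 9 and 14). The extra visits are there to show how fast effects appear and how long they last.

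**Power.** Under Sample size and power calculation, study 1 aims at a difference of at least 3 HDRS-17 points, assumes an SD of 3 points, and takes one post-treatment value per arm: "the mean scores to be 18 and 21 after Epo and placebo treatment, respectively". With 20 per arm and a two-sided 5% level, the sample "has a statistical power of 86% to detect a clinically relevant difference in HDRS-17 scores between the two treatment groups". Study 2 has the same structure: means of 56 and 52, an SD of scores of 4, 20 per arm, 86%. No baseline value, repeated visit, correlation or dropout enters either calculation.

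**Test.** Under Statistical analyses, the data are to be analysed by repeated-measures ANOVA, and "Significant interactions were analysed further with simple main effect analyses". The section does not list the visits in the ANOVA, single out week 9, or say what happens at week 9 if the interaction is not significant.

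**Strata.** Under Randomisation: "Treatment groups are stratified for age" (below 35, or 35 and over) and for gender.

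**The concern.** Three statements in one document do not fit together. The outcome is a difference at one visit, and the power is for a difference at one visit. The named test is an analysis over several visits whose follow-up step is tied to an interaction.

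A group-by-time interaction over three or four visits asks whether the two profiles differ in shape anywhere. It spends degrees of freedom on week 5, when treatment is only part-way through, and on week 14, six weeks after treatment ends. If week 9 is looked at after that test succeeds, a real week-9 effect of the planned size can be missed because the interaction fell short. With 20 patients per arm there is little margin. The reader also cannot tell which p-value will be reported as the primary result of each study.

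**Working it through.** **Inputs from the protocol article:** n = 20 per arm; difference 3 with SD 3 (study 1) and 4 with SD 4 (study 2), so d = 1 in both; two-sided 5%; the visits listed above.

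**Assumed, because the document does not give them:** equal between-visit correlation ρ of 0.3, 0.5 or 0.7; equal variances; no baseline difference; no dropout; an effect of half size at week 5; an effect of half or full size at week 14.

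**1. The stated 86%.** For a two-sample t-test the noncentrality is d·√(n/2) = 1·√10 = 3.162 on 38 df. Power is 86.9%, so the stated figure is that of a single-visit comparison. The normal approximation gives 88.5% and a one-sided t-test 92.8%; neither matches as well.

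**2. ANOVA with baseline and week 9 only.** The interaction is then a t-test on change. The SD of change is SD·√(2(1−ρ)), so the noncentrality is √10/√(2(1−ρ)) = 2.673 / 3.162 / 4.082. Power is 74 / 87 / 98%. It meets the stated figure only near ρ = 0.5, where the SD of change equals the SD of scores.

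**3. ANOVA with all scheduled visits, interaction test alone.** The noncentrality is λ = (n/2)·Σ(dₜ − d̄)²/(1−ρ), with T−1 and 38(T−1) df, where dₜ is the group difference in SD units at each of T visits.

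| Study and profile of differences | Σ(dₜ − d̄)² | λ at ρ 0.3 / 0.5 / 0.7 | Power |
|---|---|---|---|
| 1: 0, 0.5, 1, 0.5 | 0.500 | 7.14 / 10.0 / 16.7 | 58 / 75 / 94% |
| 1: 0, 0.5, 1, 1 | 0.6875 | 9.82 / 13.75 / 22.9 | 74 / 88 / 99% |
| 2: 0, 1, 0.5 | 0.500 | 7.14 / 10.0 / 16.7 | 65 / 80 / 96% |
| 2: 0, 1, 1 | 0.667 | 9.52 / 13.3 / 22.2 | 78 / 90 / 99% |

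**4. Both steps: significant interaction, then a significant week-9 group difference.** These are simulated, and repeat runs agree to about one percentage point.

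| Study and profile of differences | ρ 0.3 / 0.5 / 0.7 |
|---|---|
| 1: half effect at weeks 5 and 14 | 56 / 68 / 82% |
| 1: half at week 5, full at week 14 | 66 / 78 / 85% |
| 2: half effect at week 14 | 60 / 73 / 85% |
| 2: full effect at week 14 | 70 / 79 / 86% |

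The two-step rule cannot beat the week-9 t-test that forms its second step, so 86.9% is its ceiling.

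**5. Week-9 comparison adjusted for baseline.** The residual SD is SD·√(1−ρ²), so the noncentrality is about √10/√(1−ρ²) = 3.315 / 3.651 / 4.428, which gives roughly 90 / 94 / 99%. Simulation, which allows for chance baseline imbalance, gives 88–90 / 93–94 / 99%. The effects at weeks 5 and 14 play no part.

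**The case against.** A reader might infer that the plan enters every visit and forbids a look at week 9 unless the interaction is significant. The text says neither. It lists no visits, and the follow-up sentence does not contain the word only. Reading it as a gate is natural, but it is a reading.

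A milder reading is available. All primary, secondary and tertiary outcomes are set at week 9, and the study 2 effect is worded as a difference in change, which fits an ANOVA on baseline and week 9. The interaction is then itself the week-9 change contrast and no harmful gate exists. This stands as a possibility. It does not rescue the power figure, which would need an assumed correlation and equals 86% only near 0.5.

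A reader might also infer that the trial is underpowered. The documents do not support that in general: the all-visit interaction test alone exceeds 86% at a correlation of 0.7, and the two-step loss is small there.

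It is also fair that this is a condensed article. Leaving baseline and stratum covariates to an analysis plan is ordinary, and a change analysis is valid in a randomised trial. Their absence is therefore not counted as an error; they appear below only as part of the remedy.

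**Conclusion.** The mismatch stands. The outcome and the 86% both refer to one week-9 comparison, and the named analysis does not identify that comparison as the deciding test. This follows from the text alone and rests on no assumption.

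The size of the consequence does rest on assumptions. Under the all-visit, two-step reading, power ranges from about 56% to 86% over the correlations and week-14 effects shown. Under the two-visit reading it ranges from 74% to 98%. A baseline-adjusted week-9 test gives about 88% to 99% and does as well or better in every case examined.

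This is an ambiguity worth settling before results are known, with moderate confidence as to its effect. It is not proof of a faulty test.

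**What to change.** Before unblinding, state the primary analysis of each study as one treatment contrast at week 9. Use ANCOVA, or the week-9 contrast of a mixed model, adjusted for baseline score, age stratum (under 35, or 35 and over) and gender. Report the estimate, 95% confidence interval and two-sided p-value whatever the interaction shows. Keep the profile over the remaining visits as a secondary description of onset and persistence. Restate the power as that of this week-9 test with its assumed correlation, or keep 86% and label it as the conservative, unadjusted figure.

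The cost is analysis wording and three covariate degrees of freedom. The baseline and week-9 measurements are already scheduled. Under Current trial status, enrolment was still open (21 randomised by October 2010, recruitment planned to September 2013), so no new measurements are needed.

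### As written, the deciding ITT analysis has no stated way to differ from the complete-data PP analysis, because the only model named is repeated measures ANOVA

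*Protocol article*

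**What the plan says.** The Statistical analyses section of the protocol article fixes four things.

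- **Model and data:** "Data will be collected until dropout from all randomised patients and analysed using repeated measures analysis of variance (ANOVA". No other model is named. The software is SPSS, with no procedure given.
- **Analysis sets:** where data are missing or invalid, "we will perform Per Protocol (PP) analyses for complete data sets and Intention to Treat (ITT) analysis". PP is thus tied to completeness of data.
- **Decision rule:** if the two analyses disagree, "the outcome of the ITT analysis will be regarded as the result of the study".
- **Left open:** which visits are the within-patient levels of the ANOVA, and how a patient with incomplete data enters the ITT analysis.

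Under Outcome assessments, the primary outcome of study 1 is "depression severity as measured with the HDRS-17 [1] at week 9"; in study 2, "the primary outcome is memory performance measured with the RAVLT at week 9". The same section schedules mood ratings at baseline and weeks 5, 9 and 14 (four visits), and neuropsychological tests at baseline and weeks 9 and 14 (three visits).

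**The concern.** Model, analysis sets and decision rule do not fit together. Classical repeated measures ANOVA needs a value at every visit in the model and deletes a patient who lacks one. Run on all randomised patients with nothing imputed, it keeps the complete data sets, which is what the plan calls PP. The rule that ITT prevails would then choose between two nearly identical analyses. If the rule does act, an imputation method that the article does not name determines the result of the trial.

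Three consequences follow.

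- **Bias.** Under Safety parameters and monitoring, patients whose thrombocytes stay high or reticulocytes stay low are withdrawn. Safety precautions describes reticulocytes as the first indicator of pure red cell aplasia, which Safety profile of Epo lists as an Epo effect. Withdrawal may therefore depend on treatment, and completers need not remain comparable between arms.
- **Lost primary data.** Depending on the visits modelled, a patient with an observed week-9 score could be dropped for missing week 5 or week 14.
- **Meaning of PP.** A patient who missed infusions but attended every assessment counts as PP. A fully treated patient who missed one assessment does not.

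**Working it through.** **1. The plan's own power.** Inputs from Sample size and power calculation: 20 per arm, two-sided 5%, difference 3 with SD 3 (HDRS-17) and difference 4 with SD 4 (RAVLT), so d = 1 in both studies. For a two-sample t-test with n per arm, the noncentrality is d × √(n/2), with 2n − 2 degrees of freedom. At n = 20 this is √10 = 3.16 with 38 df, giving 86.9%. The stated 86% is reproduced and is not in dispute. It presumes that all 40 patients are analysed.

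**2. Who is in each set.** With no imputation:

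| Set | Rule in the plan | Patients actually used by classical repeated measures ANOVA |
|---|---|---|
| PP | complete data sets | complete on the modelled visits |
| ITT | all randomised, data up to dropout | complete on the modelled visits |

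The two can differ only through data judged invalid or through a step that the article does not describe.

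**3. Week-9 values at risk.** This depends on the visits modelled. If only baseline and week 9 enter, missing week 5 or 14 drops nobody. If all scheduled visits enter, let m be the chance that any one visit is missing, independently. The documents give no value for m; 2% to 10% is an assumption. In one study of 40, with k modelled visits, the expected number with a week-9 value is 40(1 − m), the number complete is 40(1 − m)^k, and the difference is the number dropped despite a week-9 value.

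| m | With week 9 | Complete, HDRS-17 (k = 4) | Dropped | Complete, RAVLT (k = 3) | Dropped |
|---|---|---|---|---|---|
| 2% | 39.2 | 36.9 | 2.3 | 37.6 | 1.6 |
| 5% | 38.0 | 32.6 | 5.4 | 34.3 | 3.7 |
| 10% | 36.0 | 26.2 | 9.8 | 29.2 | 6.8 |

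This lets the baseline visit be missing too. If baseline is always obtained, the number dropped is 40(1 − m) × [1 − (1 − m)^(k−2)]: 1.6, 3.7 and 6.8 for HDRS-17, and 0.8, 1.9 and 3.6 for RAVLT.

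**4. Power with fewer analysed patients.** The formula of step 1, with illustrative losses of 10% and 20%:

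| n per arm | Noncentrality | df | Power |
|---|---|---|---|
| 20 | 3.16 | 38 | 86.9% |
| 18 | 3.00 | 34 | 83.0% |
| 16 | 2.83 | 30 | 78.1% |

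**5. Dropout so far.** Current trial status reports 1 of 21 randomised (1/21 = 4.8%) leaving after week 5 for abnormal laboratory results. Neither the study nor the arm is given.

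**The case against.** The strongest reply is that the plan contrasts ITT with complete data sets and provides for disagreement between them. That makes sense only if its authors meant incomplete patients to enter ITT somehow. A journal article may leave the mechanism to the full protocol or analysis plan, which are not shown. Naming SPSS settles nothing, because SPSS also fits mixed models. This stands as far as it goes: the missing detail alone is not the fault. The fault is that the one model the article commits to cannot deliver the analysis it makes decisive.

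A reader might infer more than the documents support:

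- *That ITT certainly equals PP.* It does so only if nothing is imputed.
- *That a patient without week 14 is necessarily lost from the primary analysis.* The modelled visits are not stated. A baseline and week-9 ANOVA fits the week-9 outcomes and the framing of the RAVLT effect as a difference in change.
- *That the reported dropout shows a valid week-9 score being discarded.* That patient left after week 5 and presumably has no week-9 score. No documented patient shows this loss.
- *That the fall from 86.9% to 78.1% is the price of ANOVA.* A patient lost before week 9 costs information under any method.

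It is also fair that running ITT only when data are missing or invalid does little harm in itself: with PP defined by completeness, the two sets coincide otherwise.

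**Conclusion.** The point holds conditionally. Unless an imputation not stated in the article is used, the deciding ITT analysis contains essentially the same patients as PP and the override rule cannot act. The definition of PP by completeness is in the text and needs correction either way.

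Whether valid week-9 outcomes are lost depends on the visits modelled: none through a missed week 5 or 14 if only baseline and week 9 enter; about 2 to 10 of 40 (HDRS-17) or 2 to 7 of 40 (RAVLT) if all visits enter, at an assumed 2% to 10% missing per visit, and fewer if baseline is always observed. The power figures illustrate the effect of a smaller analysed sample and do not measure the gain from a better model. The bias is a risk with no size attached: withdrawals may depend on treatment, but the documents do not show that they do. The matter is worth correcting and does not undermine the design.

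**What to change.** Make the primary analysis in each study a likelihood-based mixed model for repeated measures, on all randomised patients in the arm to which they were randomised. Include baseline score, the age and gender strata, treatment, visit and treatment-by-visit, and take the week-9 treatment contrast as the primary result. Run it in all cases, so that no tie-break is needed. Define PP by adherence to the protocol, including infusions received, and report it as supportive only.

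The model assumes that data are missing at random. Add one sensitivity analysis for missing week-9 values, for example one that gives missing values in the Epo arm placebo-like outcomes. This matters most in study 2: RAVLT has no assessment between baseline and week 9, so for a patient who leaves before week 9 the model has no later score to draw on.

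The cost is a change of wording. SPSS can fit the model, and neither visits nor sample size change.
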